### Data analysis

Hypotheses will be tested by using one-way analysis of variance (ANOVA), followed by Tukey post-hoc tests comparing the three groups pairwise.

A reasonable approximation to a normal distribution, according to the central limit theorem, can be assumed with the calculated sample size, allowing the use of parametric analysis. Deviations of the normal distribution will be tested and appropriate transformations will be performed. Homogeneity of variance will be tested with the Levene’s test.

The primary analysis will be performed with the intent-to-treat (ITT) population. Missing data will be imputed by the next-observation-carried-backwards option for initial values and last-observation-carried-forwards option for closing values. Legs with missing initial and closing data for the primary endpoint will be deleted from the analysis. The average values of both legs will be evaluated for patients with bilateral assessable measurements. For unilateral results, only the evaluable leg will be included in the analysis. The comparison between verum needle acupuncture and placebo laser acupuncture will be undertaken for validating the overall treatment effect of acupuncture. Verum laser acupuncture and placebo laser acupuncture will be compared for validating the specific treatment effect. The comparison of needle acupuncture to verum laser acupuncture will indicate the non-specific effect of needle acupuncture. Remaining NCS outcomes will be analyzed as described for the primary outcome. Multivariate analyses of the clinical secondary outcomes (NDS, NSS, and NRS) and their correlation to NCS parameters will be performed by linear regression models.

Baseline data and clinical characteristics will be presented as mean values to assess the baseline comparability of the intervention groups. Those patients who report changes of pain medication during the study will be excluded from data analysis relating to subjective pain scales. Statistical analysis will be done with the software SPSS (IBM SPSS Statistics 22) and OriginPro 9.

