## Methods/design

### Trial design

The aim of the ACUDIN trial is to examine if acupuncture and laser acupuncture have beneficial effects on NCS parameters, clinical scores and patient’s complaints in DPN as evaluated by standardized tests. A prospective, randomized, placebo-controlled, partially double-blinded, three-armed study design has been applied to the ACUDIN trial to compare the effects of classical needle acupuncture and laser acupuncture with those of placebo laser acupuncture.

Patients will receive 10 treatments over a period of 10 weeks. Each session will last 20 min. Neurological assessment, including NCS, is performed at baseline, week 6 and week 15 (Fig. 1).

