### Randomization procedure

Recruited patients are randomized in a ratio of 1: 1: 1 into three parallel treatment groups of 60 participants: (i) classical needle acupuncture, (ii) verum laser acupuncture, and (iii) placebo laser acupuncture. Randomization is prepared beforehand with 180 identical closed envelopes, each.

containing one of the three possible group allocations and a randomly generated four-number pseudonym code for further data processing. Randomization is performed by envelope lottery immediately prior to the first treatment session by study nurse 1. Patients and practitioners are only informed about the patients’ allocation to either needle or laser treatment. However, patients do not know whether they will receive a true treatment or placebo. Group assignment will not be exposed until the final data analysis report is completed.

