## Outcome measures

### Primary endpoint

The primary endpoint is the difference of the 15-week measurement minus baseline of the sural sensory nerve action potential amplitude (sural SNAP).

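### Carrying values backwards and forwards in the primary change-score analysis biases the week-15 estimate, by up to 0.10 μV of 1 μV at the planned drop-out

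*Protocol article*

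**What the plan says.** All references are to the Protocol article.

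- **Primary endpoint:** "The primary endpoint is the difference of the 15-week measurement minus baseline of the sural sensory nerve action potential amplitude (sural SNAP").
- **Population (Data analysis):** "The primary analysis will be performed with the intent-to-treat (ITT) population".
- **Imputation (Data analysis):** "Missing data will be imputed by the next-observation-carried-backwards option for initial values and last-observation-carried-forwards option for closing values".
- **Deletion (Data analysis):** "Legs with missing initial and closing data for the primary endpoint will be deleted from the analysis".
- **Visits (Trial design):** neurological assessment with nerve conduction is "performed at baseline, week 6 and week 15".
- **Treatment period (Trial design):** "Patients will receive 10 treatments over a period of 10 weeks".
- **Randomisation (Randomization procedure):** "Randomization is performed by envelope lottery immediately prior to the first treatment session by study nurse 1".

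Data analysis also says that both legs are averaged when both can be assessed, and that a patient with results on one side contributes that side alone. It does not say whether a leg is judged assessable before or after imputation. The completed changes go into a one-way ANOVA with Tukey pairwise comparisons.

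**The concern.** The endpoint is a difference between two visits, and the rule fills either one from another visit of the same leg. With three visits there are few donors, and each has a consequence:

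- **Baseline missing, week 6 present.** The baseline becomes a value taken on treatment, so whatever was gained by week 6 is subtracted from the outcome.
- **Baseline and week 6 missing.** Week 15 is subtracted from itself, and the change is exactly 0.
- **Week 15 missing, week 6 present.** A value from the middle of the 10-week course stands in for one taken about five weeks after the course ends.
- **Week 15 and week 6 missing.** Baseline is subtracted from itself, and the change is exactly 0.

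The imputed changes are then analysed as if observed. At stake is the size of the primary estimate and, if arms lose patients at different rates, its direction of bias.

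The deletion sentence does not remove the problem. If it means that both end values are missing, single-visit legs at baseline or week 15 stay in with zero change. If it means that either is missing, it contradicts the imputation sentence.

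**Working it through.** **Inputs from the article (Sample size calculation).** Relevant difference 1 μV, SD 1.83 μV, alpha 0.05, power 0.80, 54 per arm with complete follow-up, 10% drop-out, 60 per arm.

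**Step 1: the plan's own figure.** A two-sided two-sample t-test for 1 μV with SD 1.83 has power 0.796 at 53 and 0.803 at 54 per arm, so 54 is reproduced. 54 / 0.90 = 60 per arm, or 180 in total.

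**Step 2: equal drop-out.** Let m be the share of patients whose change is imputed and k the share of the week-15 effect present at week 6. With a true difference of 1 μV and missingness unrelated to outcome:

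- all imputed changes zero: 1 − m
- week 6 carried forward to week 15: 1 − m(1 − k)
- week 6 carried back to baseline: 1 − mk

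| Imputed change | m = 10% | m = 20% |
|---|---|---|
| Exactly 0 | 0.90 μV | 0.80 μV |
| Week 6 for week 15, k = 0.3 to 0.8 | 0.93 to 0.98 μV | 0.86 to 0.96 μV |
| Week 6 for baseline, k = 0.3 to 0.8 | 0.97 to 0.92 μV | 0.94 to 0.84 μV |

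Simulation (8,000 trials per setting, 60 per arm) agrees within simulation error. The values of k and the 20% rate are assumptions; the 10% rate is the plan's. The figures take the whole patient as imputed. If only one of two averaged legs is imputed, that patient's dilution is halved.

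**Step 3: the SD.** With imputed zeros, the variance within an arm with mean change μ is (1 − m) × 1.83² + m(1 − m)μ². For m = 0.10:

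- μ = 1: 0.9 × 3.3489 + 0.09 = 3.104, SD 1.76
- μ = 0: 0.9 × 3.3489 = 3.014, SD 1.74

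The pooled SD is about 1.75 μV. The estimate and its SD shrink together.

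**Step 4: power under the planned Tukey comparison.** For 1 μV, 60 per arm and 10% missing in each arm, power is about 0.67 with zeros imputed and about 0.68 with complete cases only. With no missing data it is about 0.73.

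**Step 5: unequal drop-out, no treatment effect.** If every arm changes by c over 15 weeks and zeros are imputed, the expected active-minus-placebo difference is c × (m_placebo − m_active). All inputs here are assumptions:

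- c = −1, active 15%, placebo 5%: −1 × (0.05 − 0.15) = +0.10 μV
- c = −1, active 5%, placebo 15%: −1 × (0.15 − 0.05) = −0.10 μV
- c = −0.5, active 20%, placebo 5%: −0.5 × (0.05 − 0.20) = +0.075 μV

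The sign follows whichever arm loses more patients. In the last case the Tukey rejection rate for one active arm against placebo stays near 0.02 with or without imputation. With c = ±1 and 5% against 25%, the spurious difference is 0.20 μV and the two-sided error of an unadjusted t-test rises to about 0.10.

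**The case against.** **Size.** At the planned 10% the shift is 0.02 to 0.10 μV, and the top of that range needs every incomplete patient to have been seen at one visit only. This stands: the bias is modest.

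**Conservatism.** With equal drop-out and an effect that builds up to week 15, the rule works against the acupuncture arms. This is true under those two conditions, but the plan secures neither. If the effect peaked on treatment and faded, k would exceed 1 and carry-forward would overstate it. Unequal drop-out is plausible, since needle-arm patients know that they are being needled and the listed acupuncture harms differ from those for laser.

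**Baseline carry-back is rare.** This also stands. Pathologic nerve conduction results are an inclusion criterion, so a wholly missing baseline should be uncommon. Most of the effect comes from the closing-value rule.

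**Stronger readings the documents do not support:**

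- *The rule badly damages power.* With 20% drop-out in the active arms and 10% on placebo (assumed), Tukey power with imputed zeros is about 0.58. It is already about 0.73 with no missing data and about 0.65 with complete cases, so the rule accounts for only about 7 points.
- *The rule creates false positives.* This needs both a sizeable common change and markedly unequal drop-out, neither of which the article gives.
- *Missing legs are unrecordable potentials, so the largest recoveries or losses are scored as no change.* The article does not say that an absent potential is treated as missing; it may be recorded as 0 μV.
- *A measured leg is always averaged with an imputed one.* The article already provides for using the one assessable leg. Only its order relative to imputation is unclear.

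**Conclusion.** The concern holds as a bias in the primary estimate caused by a rule that the article states. Two consequences follow from the visit schedule without further assumption: every carried-back baseline is post-randomisation, and every leg seen only at baseline or only at week 15 is given a change of exactly 0. A general claim that the rule forces changes towards zero goes too far, because a leg filled from week 6 gets a part-period change whose bias depends on an unknown time course.

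At the plan's 10% drop-out, the dilution is 0.10 μV of 1.00 μV at most when drop-out is equal and the effect does not reverse, and about 0.02 to 0.08 μV if week 6 is the donor and holds 30 to 80% of the effect. With unequal drop-out and a common change over time, the bias can favour either arm. Power at equal 10% drop-out is nearly the same as with complete cases. The artificially smaller SD means that the dilution would not show as lost precision.

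**What to change.** - Make the primary analysis a likelihood-based repeated-measures model on the observed baseline, week-6 and week-15 values, with arm-by-visit terms, and report the pairwise week-15 contrasts. Holding the baseline mean equal across arms lets a patient without a baseline still contribute. Multiple imputation is an acceptable alternative.
- State that a baseline value is not filled from a visit after randomisation.
- State that the rule for using the single assessable leg is applied before any imputation, and reword the deletion sentence so that it has one meaning.
- Keep the carry-back and carry-forward analysis as a sensitivity analysis.

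The cost is a change of wording and slightly more modelling, with no new data; the named SPSS software fits mixed models. The downside is reliance on data being missing at random. The change should be fixed before treatment groups are matched to the outcome data.

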### Questionnaires to collect participants’ opinions

Common DPN-related symptoms will be recorded weekly by questionnaires using 11-point numeric rating scales (NRS) with the terminal descriptors “no complaint” and “worst complaint possible”. Whilst NRS are well validated for painful conditions [53], our questionnaires assess not only neuropathic pain but also tingling, burning pain, feeling of heat, feeling of cold, cramps, numbness, gait impairment, impairment of daily activities, sleep disturbances, and complaint frequency.

Table 1 summarizes the plan of data collection.

**Table 1 Tab1:** Baseline and outcome parameters

	Baseline parameter	Blood parameter	Neurological assessment	NCS^f^ Parameter	Subjective Score
Week 0	Age Gender Weight Size Comorbidity Medication Duration of disease (Diabetes and DPN)	HbA_1c_^a^	Clinical examination NSS NDS^c^	Bilateral amplitudes and NCV^b^of nn. surales and tibiales	NRS^d^
Week 6			Clinical examination NSS^e^ NDS	Bilateral amplitudes and NCV of nn. surales and tibiales	NRS
Week 15	Change of medication	HbA_1c_	Clinical examination NSS NDS	Bilateral amplitudes and NCV of nn. surales and tibiales	NRS Adverse events
Weekly (treatment 1–10)	Change of medication				NRS Adverse events

^a^HbA1c= glycated hemoglobin; ^b^NCV = nerve conduction velocity; ^c^NDS = neuropathy deficit score; ^d^NRS = numeric rating scale; ^e^NSS = neuropathy symptom score; ^f^NCS = nerve conduction studies

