### Key secondary endpoints

Secondary endpoints are the differences of the 15-week measurement minus baseline of the remaining NCS measurements:

the sural sensory nerve conduction velocity (sural SNCV),

tibial motor nerve action potential amplitude (tibial MNAP),

tibial motor nerve conduction velocity (tibial MNCV).

Additional secondary endpoints will be obtained from the questionnaires:

The differences in the 15-week measurement minus baseline of NDS, NSS, and NRS scores.

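### Dropping every patient who changes pain medication from the pain-scale analyses breaks the randomised comparison for those secondary endpoints; keep all randomised patients in the main analysis (should fix).

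*Protocol article*

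**What the plan says.** The rule is in the protocol article under Data analysis: "Those patients who report changes of pain medication during the study will be excluded from data analysis relating to subjective pain scales". It covers any reported change during the study. No analysis that retains these patients is described.

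Four other places bear on it:

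- **Endpoint.** Key secondary endpoints lists, after the nerve conduction measures and as additional endpoints, "The differences in the 15-week measurement minus baseline of NDS, NSS, and NRS scores". The questionnaire section says that "our questionnaires assess not only neuropathic pain but also tingling, burning pain" and several other complaints, so pain is only part of the NRS set.
- **Timing.** Under Randomization procedure, "Randomization is performed by envelope lottery immediately prior to the first treatment session by study nurse 1". Table 1 records medication changes at week 15 and in the row "Weekly (treatment 1–10) Change of medication". The excluding event therefore follows allocation.
- **Link to pain.** The Background says that several drug classes palliate neuropathic pain and paresthesia.
- **Population and missing data.** "The primary analysis will be performed with the intent-to-treat (ITT) population"; this sentence speaks of the primary analysis only. The imputation rule, "last-observation-carried-forwards option for closing values", deals with missing values and does not bring excluded patients back.

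**The concern.** A patient may add pain medication because pain persists under the allocated treatment, or reduce it because pain has eased. The rule deletes both. If the active treatments relieve symptoms, as the trial hypothesises, the frequency and direction of medication changes should differ between arms. The exclusion then conditions on something that treatment can influence, and randomisation no longer protects the comparison of those left.

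At stake is the reading of the pain results. A real effect could be understated, or a difference could appear that treatment did not cause. The analysis set also shrinks.

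**Working it through.** The plan gives no figure for this rule: no SD of the NRS change, no expected pain effect, no rate of medication change. Its sample size rests on sural SNAP alone and is not touched. Every input below is therefore an assumption, chosen to show the range.

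**Set-up.** Let Y be the NRS change (week 15 minus baseline; negative is improvement), normal with SD 2. The placebo mean is -0.5 and the active mean -1.5, a true difference of -1.0. A patient changes medication with probability 0.40 if Y > 0.5 (worse) or Y < -3 (marked improvement), and 0.05 otherwise. Medication has no effect on pain at this stage.

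**Formula.** With p the probability of each zone, e the partial mean (the integral of y times the density over that zone) and k the probability of being kept (0.60, 0.95, 0.60), retained mean = Σke / Σkp.

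| Arm | p: improved, middle, worse | e: improved, middle, worse |
|---|---|---|
| Placebo | 0.106, 0.586, 0.309 | -0.418, -0.632, 0.550 |
| Active | 0.227, 0.615, 0.159 | -0.942, -0.804, 0.246 |

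- Placebo: kept 0.063 + 0.557 + 0.185 = 0.805. Mean (-0.251 - 0.600 + 0.330)/0.805 = -0.647.
- Active: kept 0.136 + 0.584 + 0.095 = 0.815. Mean (-0.565 - 0.764 + 0.148)/0.815 = -1.449.
- Estimated difference: -1.449 + 0.647 = **-0.80**, with about 19% of patients discarded.

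**Variants by the same formula.**

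- Only worsening raises the rate to 0.40 (k = 0.95, 0.95, 0.60): -1.689 + 0.793 = **-0.90**. Discarded: 15.8% placebo, 10.5% active.
- Only marked improvement raises it (k = 0.60, 0.95, 0.95): -1.258 + 0.360 = **-0.90**. Discarded: 8.7% placebo, 12.9% active.
- No true effect, same mechanism in both arms: the retained means are equal, so the bias is **0**.
- No true effect, placebo patients change on worsening and active patients on improvement: -0.360 + 0.793 = **+0.43**, a spurious difference against the active arm. With the mechanisms swapped it is -0.43, in its favour.

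**A different model.** Let the log-odds of a change depend linearly on Y, with slope 1 to 2 per SD. For a true -1.0 the estimates are:

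- Worsening prompts the change: -0.94 to -0.87 at a 10% placebo change rate, and -0.87 to -0.74 at 30%.
- Improvement prompts the change: -0.92 to -0.81 at 10%, and -0.88 to -0.73 at 20%.
- Slope 0 (changes unrelated to pain): no bias.

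**Adding a drug effect.** Take the worsening-only case and let a medication change lower the NRS by D points. The all-patient difference is -1.0 + D × (0.158 - 0.105), which is about -0.95, -0.90 and -0.84 for D = 1, 2 and 3. The exclusion gives -0.90 in the same case.

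**The case against.** The strongest defence is that the rule has a purpose: changed medication alters the pain score, so a comparison that includes it no longer isolates acupuncture. That is a fair concern, and the last calculation bears it out. Measured against the effect that would be seen without medication, the all-patient analysis is not clearly less attenuated than the exclusion. The exclusion does not meet the concern, though, because it exchanges possible dilution for selection. The all-patient analysis preserves randomisation and answers a well-defined question: the effect of allocation, including any change of medication that follows.

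Four stronger readings are tempting, and the documents do not support them.

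- *That medication change is driven by the outcome.* A reader might infer this from the Background, but the article does not say why patients change medication. The Discussion mentions drug side effects, which are another possible reason. The link is plausible, not established.
- *That the rule contradicts intention-to-treat.* It does not; the ITT sentence covers the primary analysis only.
- *That the bias is larger in the needle comparison.* Patients know whether they receive needles or laser, and this could affect medication use. It could do so in either direction, and nothing in the documents gives its size.
- *That the rule threatens the trial's conclusion or manufactures a benefit.* The stated hypotheses concern sural SNAP. Under a mechanism shared by all arms, the modelled bias shrinks a true effect and is zero under the null.

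**Conclusion.** The point holds for the pain items of the NRS. The article fixes, as the only described analysis of those scales, a subset defined by an event after randomisation that is plausibly related to pain and so to treatment. This is a stated rule, not a detail left to another document.

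The documents determine neither the size nor the direction of the bias. Under the threshold assumptions a true -1.0 is estimated as about -0.80 to -0.90, and the logistic model widens this to about -0.94 to -0.73. A spurious difference of about 0.4 points can arise in either direction if the mechanisms differ by arm. All of these figures leave out any drug effect, so the shortfall from -1.0 is not simply what the change of analysis would recover.

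Because only additional secondary endpoints are affected, and the primary and other nerve conduction analyses stand, this is a should-fix.

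**What to change.** Replace the exclusion sentence under Data analysis with three provisions:

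1. The main analysis of the pain scales includes all randomised patients, whether or not pain medication changed, and names the NRS items concerned.
2. The numbers of patients who increased and who decreased pain medication are tabulated by arm. Table 1 already schedules "Change of medication" at each treatment and at week 15, and medication at baseline, so no new visit is needed. Table 1 does not show whether the direction of change is recorded, so this should be checked in the source records.
3. The analysis without patients who changed medication is kept as a sensitivity analysis and labelled as such.

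The cost is a change of wording and one table. The downside is that the all-patient estimate includes the effect of any medication change and can be diluted by it: in the worsening-only example, to about -0.95 to -0.84 for a true -1.0 if added drugs lower the NRS by 1 to 3 points. The by-arm table lets the reader judge whether that is likely.

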### Sample size calculation

An average difference of 1 μV was considered functionally relevant for sural SNAP [54]. On the basis of a pilot study [24], a pooled standard deviation of 1.83 μV was calculated. By assuming that this standard deviation represents the best estimate of the actual standard deviation for each of the three groups in a regular three-arm parallel RCT design with complete follow-up, 54 patients per arm are required to detect the above difference for sural SNAP with an alpha of 0.05 and a power of 0.8. The assumption of a conservative 10% drop-out rate for patients randomized to any of the three arms increases the sample size to 60 patient per arm or 180 patients in total.

Power evaluations were performed with statistical analysis system (SAS) 9.2 for the above described statistical analysis (one-way ANOVA) and followed by post-hoc testing for the primary outcome.

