## Statistical analysis

Major hypotheses tested are:

H0:

The differences of the 15-week measurements minus baseline of sural SNAP in the two groups with classical needle acupuncture or laser acupuncture are the same or smaller as in the control group.

vs.

H1:

The differences of the 15-week measurement minus baseline of sural SNAP in the groups with classical needle acupuncture or laser acupuncture are larger than in the control group.

In addition, for the two types of acupuncture treatment, two-sided hypotheses will be tested.

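### The 80% power stated for 54 patients per arm fits one unadjusted pairwise test; each planned Tukey comparison has about 68% power for the same 1 μV difference

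*Protocol article*

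**What the plan says.** The Sample size calculation section gives the planning inputs: "An average difference of 1 μV was considered functionally relevant for sural SNAP", and from a pilot study "a pooled standard deviation of 1.83 μV was calculated", taken to hold in each of the three groups. It concludes that "54 patients per arm are required to detect the above difference for sural SNAP with an alpha of 0.05 and a power of 0.8", and raises 54 to 60 per arm for 10% drop-out. It then names the analysis behind the figure: "Power evaluations were performed with statistical analysis system (SAS) 9.2 for the above described statistical analysis (one-way ANOVA"), with post-hoc testing of the primary outcome to follow.

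The Data analysis section specifies that analysis as a one-way ANOVA "followed by Tukey post-hoc tests comparing the three groups pairwise". It gives each pair its own reading: needle versus placebo laser for the overall effect of acupuncture, verum laser versus placebo laser for the specific effect, and needle versus verum laser for the non-specific effect of needling.

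The Statistical analysis section words the null hypothesis for active versus control in one direction (changes that "are the same or smaller as in the control group"), while "for the two types of acupuncture treatment, two-sided hypotheses will be tested". The sample size section does not state whether its alpha is one- or two-sided, what pattern of three means it assumes, or whether the 80% is for the overall F-test, for any pair or for each pair.

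**The concern.** The calculation uses one difference, one standard deviation and an alpha of 0.05, which are the inputs of an ordinary two-group comparison. Tukey's procedure protects the error rate over three pairs by raising the critical value for each, so at the same sample size each comparison has less power. If the 80% was obtained without that adjustment, it does not describe the analysis to which the document attributes it.

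The trial's conclusions come from the individual pairs. A significant F-test says neither whether needling beats placebo nor whether active laser does. If power per pair is well below 80%, readers will give a non-significant comparison more weight than it can bear. This matters most for verum versus placebo laser, the one double-blind comparison and the one meant to isolate the specific effect.

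**Working it through.** **Inputs** (Sample size calculation section): difference 1 μV, SD 1.83 μV, alpha 0.05, power 0.80, 54 evaluable per arm, 10% drop-out. Test (Data analysis section): one-way ANOVA, then Tukey on all three pairs. Allocation 1:1:1 (Randomization procedure section).

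**1. Reproducing the plan's figure.** The standard error of a difference between two arms is 1.83 × √(2/54) = 0.352 μV, so the noncentrality is 1/0.352 = 2.84.

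- Two-sided 5% t-test on two groups, df = 2 × 54 − 2 = 106, critical value 1.98: power 80.3%. At 53 per arm it is 79.6%, so 54 is the smallest sufficient number.
- The same unadjusted contrast with the three-group error term, df = 3 × 54 − 3 = 159, critical value 1.97: power 80.6%. The smallest number is again 54.
- Drop-out: 54/(1 − 0.10) = 60 per arm, 180 in total, as stated.
- A one-sided 5% t-test would need only 43, so that is not the source of the figure.

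**2. The planned Tukey comparison.** The critical value on the t scale is q(0.95; 3, 3n − 3)/√2. At n = 54 this is 3.346/√2 = 2.366. Power for a named pair that truly differs by 1 μV, from the noncentral t distribution:

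| Evaluable per arm | Noncentrality | Critical value | Power, named pair |
|---|---|---|---|
| 54 | 2.84 | 2.366 | 68.2% |
| 60 | 2.99 | 2.364 | 73.5% |
| 69 | 3.21 | 2.361 | 80.1% |

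At 68 per arm the power is 79.5%, so 69 is the smallest number. With 10% drop-out, 69/0.90 = 76.7, rounded up to 77 per arm or 231 in total. Also requiring a significant F-test before reading the Tukey pair lowers 68.2% slightly, to 67–68%.

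At 54 per arm, a Tukey comparison reaches 80% power at a difference of about 1.13 μV (79.9% at 1.13, 80.7% at 1.14).

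**3. The overall F-test.** The noncentrality is n × Σ(mean − grand mean)²/SD².

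| Means (μV) | Power at 54 per arm | Smallest n for 80% |
|---|---|---|
| (0, 1, 1) or (0, 0, 1) | 83.7% | 50 |
| (0, 0.5, 1) | 71.2% | 66 |

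Neither of these usual planning patterns leads to 54.

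**4. Joint results if both active arms differ from placebo by 1 μV**, at 54 per arm under Tukey (simulation, 400,000 runs): at least one active arm beats placebo, 82.8%; both do, 53.5%.

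**The case against.** The strongest reply is that the protocol never says the 80% is power per pair. The alternative hypothesis speaks of needle or laser, and if both arms work by 1 μV, at least one Tukey comparison against placebo succeeds with 82.8% probability and the F-test with 83.7%. Both exceed the stated figure. This stands as a fact and belongs in the corrected text. It does not rescue the statement: it requires both treatments to work. If only one does, the chance for that pair is again 68%, and the Data analysis section draws a separate conclusion from each pair.

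A second reply is that the comparisons with placebo are worded one-sided. If that is approximated by running Tukey at a two-sided 10% level (critical value 2.07), power for a named pair at 54 per arm is 77.9%. That is much nearer to 80% but still short, and the document does not describe such a procedure. The 68% does rest on Tukey at the usual two-sided 5% level.

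Third, that 54 came from a t-test is inferred from an exact match. Other routes exist: one-sided 2.5% for each of two comparisons with placebo also gives 54, a one-sided Dunnett test would have 81.7% power at 54, and an F-test with means such as (0, 0.92, 1) needs exactly 54. The first two use methods the document does not name, and the third is contrived. The origin of the number therefore cannot be proved, but its mismatch with Tukey does not depend on it.

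Finally, the error does not touch type I error or the validity of the analysis, and confidence intervals will show the precision achieved. That is true, and it is why the remedy is limited to the wording.

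**Conclusion.** The concern holds. On the protocol's own inputs, 54 evaluable patients per arm give 80.3% power for one unadjusted two-sided comparison, but 68.2% for a named pair under the Tukey procedure that the protocol specifies, a shortfall of about 12 percentage points. If imputation lets all 60 per arm be analysed with the same effect and SD, the figure is 73.5%, still below 80%. This assumes a common SD of 1.83 μV, a true difference of 1 μV and Tukey at two-sided 5%. A one-sided reading, approximated by Tukey at 10%, would bring 54 per arm to about 78%. The stated power should not stand as attributed.

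**What to change.** Keep 180 patients and the Tukey tests, and correct the Sample size calculation section. Suggested text: 'With a standard deviation of 1.83 μV and a true difference of 1 μV, 54 evaluable patients per arm give 80% power for one unadjusted two-sided pairwise comparison at the 5% level, and about 68% power for each comparison under the planned Tukey procedure. The difference detectable with 80% power under Tukey is about 1.13 μV. If both active arms differ from placebo by 1 μV, the power to show this for at least one of them is about 83%, and for both about 53%.'

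If the sponsor changes the test procedure instead, for example to one limited to the two comparisons with placebo, the section should state the power of that procedure and whether it is one- or two-sided.

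The cost is wording, and a less favourable stated power. No patients are added; restoring 80% per Tukey comparison by sample size would take 231 patients, 51 more than planned.
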